### Assessment and outcomes measures

3.5

All assessments will occur at baseline, post-treatment (month 6), and 6-month follow-up (month 12). Both parents and children will participate in these assessments. Assessments will include anthropometry and self-report questionnaires. Parents participating in the study will be asked to complete assessments on their readiness to engage in weight control behaviors [21,22], self-efficacy to lose weight [21,23], and empowerment to access resources for healthy weight [24]. Parents will also report on their behaviors that support child weight loss efforts [25], and potential self-regulatory mediator variables such as goal setting and adherence to GSH recommendations [[26], [27], [28], [29], [30], [31], [32], [33], [34]]. Finally, parents will report on their child's dietary and physical activity behaviors, and provide information on resources utilization for the cost effectiveness analysis. Medical record abstraction will occur at the end of the study to obtain additional information regarding documented anthropometrics and health care utilization. Data collection will be conducted by trained staff and supervised by the principle investigator.

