#### Measurements (Table 1)

3.6.1

Anthropometry (child and parent). Child and parent height will be measured using a portable Schorr height board (Schorr Inc, Olney, MD) in duplicate. Height will be recorded to the nearest 0.1 cm for both trials, and the average of the 2 values used for analysis. Body weight in kilograms will be measured in duplicate on a Tanita Digital Scale (model WB-110A). Body weight will be recorded to the nearest 0.1 kg and the average of the 2 values used for analysis. Height and weight will be converted to body mass index (BMI = [kg/m2]). Since children are growing, BMI will be translated to BMI for age percentile score using the CDC growth charts [35,36] and to standardized age and gender referenced BMI (BMI Z-scores) [37].

**Table 1 tbl1:** Schedule of assessments and measures.

	Measure	Baseline	Post-treatment	6-Month Follow-up
Anthropometry	Height/Weight	X	X	X
Demographics	Demographics and Medical History questions	X		
Parent assessments	Parent Importance, Confidence, & Readiness questionnaire [21] Lifestyle Behavior Checklist (Confidence scale) [23] Parent Resource Empowerment Scale [24] Activity Support Scale [25]	X X X X	X X X X	X X X X
Child Lifestyle Behaviors	Dietary History and Eating Behaviors Godin Leisure Time Exercise Questionnaire [41]	X X	X X	X X
Parent support & weight control behaviors	Frequency of self-monitoring behaviors		X	X
	Parent report of adherence to treatment recommendations		X	X
Enrollment/attendance, Treatment Adherence, Acceptability	Enrollment and Attendance (weekly assessment) Self-monitoring in habit books (weekly assessment) Acceptability		X X	X X X
Cost-effectiveness	Family utilization & cost data Administrative data	X X	X X	X X

Demographic Characteristics (baseline only). At the baseline assessment, parents will complete demographic questionnaires that include items on racial/ethnic identity, sex, income, education, marital status, health history, and medication use.

Parent Importance, Confidence, and Readiness for Change Questionnaire: This questionnaire is a self-report measure that assesses motivation for behavioral lifestyle change. It contains three subscales: importance of change, confidence to make changes, and readiness to change. In a weight control study for children age 7–13 years old and their parents, parental confidence predicted premature participant dropout, early treatment response (5-week child weight loss) and child weight loss at post-treatment [21].

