## Data analysis

5

5.1. This study is a pragmatic randomized control trial using a one-to-one randomization ratio within each clinic, randomizing at the level of the individual. First, we will track the number of sessions each family attended within each group and examine if there is a difference in the proportion of sessions attended between groups using a generalized linear model (binomial family). For our second primary outcome, we will estimate between-group differences (GSH vs FBT) in BMI percentile/z-score (our second primary outcome) over 6- and 12-month assessments using linear mixed effects (LME) analysis adjusting for corresponding baseline BMI percentile/z-score values. BMI z-score is calculated using the formula: [(BMI/M)^L^ −1]/(L x S). (M = median; L = power in the Box-Cox transformation; S = generalized coefficient of variation; values vary based on age in months of the child) All models will adjust for standard patient characteristics (age, race/ethnicity, sex, insurance type) as planned covariates and any differential effects across clinics (i.e., main effect rather than random effect given limited number of clinics).

As a secondary analysis, we will assess the degree to which treatment assignment (GSH vs. FBT) was associated with change in proposed mediators (considered outcomes in these analyses) including child lifestyle behaviors (e.g., eating and physical activity behaviors), parent self-efficacy, parent empowerment, and parent support behaviors (e.g., parent monitoring, adherence to treatment recommendations) using LME models. For mediation modeling, we first will estimate the effect of allocation on a change in proposed mediators (path ‘a’) at 6-months with adjustment for corresponding baseline values. If significant, we will then add baseline and 6-month terms for mediators to the LME model examining their relationship to the primary outcome of BMI percentile/z-score. The indirect effect of group allocation on BMI percentile/z-score through changes in mediators (path ‘b’) will be computed using a product of coefficients method (path ‘a*b’) along with bootstrap confidence intervals. As an adjunct to the primary analyses, we will also explore attendance patterns using a cox proportional hazards regression model to examine predictors of attrition, defined as missing 3 or more consecutive sessions.

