5.2. Cost-effectiveness analysis: The cost-effectiveness analysis (CEA) will follow well-established guidelines developed by Drummond et al. [69] and Haddix et al. [70] and include identification of all relevant costs and consequences for each of the interventions and alternatives, accurate measurement in appropriate effectiveness units, sound valuation, and sensitivity analysis to test uncertainties. The final outcome of the CEA in this study is the cost per BMI unit reduced, evaluating the incremental differences between cost and effectiveness in the GSH model and usual care. The precision of the incremental cost-effectiveness ratio (ICER) will be investigated through sensitivity analyses. To account for the non-parametric nature of the data, we will use bootstrap to create confidence intervals for the mean costs and effectiveness for the comparison. ICER will be developed using the nonparametric permutation. A scatter plot of 5000 bootstrapped ICER will be generated by drawing a random sample with replacement [71]. The CEA results will be presented in a cost-effectiveness acceptability curve. The uncertainty of the parameters will be explored in sensitivity analysis.

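### Section 5.2 bootstraps mean costs and effects with no baseline adjustment named, which leaves some precision unused, mainly in the incremental cost

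*Protocol article*

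**What the plan says.** Section 5.2 of the protocol article defines the endpoint of the economic analysis: "The final outcome of the CEA in this study is the cost per BMI unit reduced", with the comparison made by "evaluating the incremental differences between cost and effectiveness in the GSH model and usual care". For uncertainty it states "we will use bootstrap to create confidence intervals for the mean costs and effectiveness for the comparison", giving the non-parametric nature of the data as the reason, and then "A scatter plot of 5000 bootstrapped ICER will be generated by drawing a random sample with replacement". An acceptability curve and sensitivity analyses follow. No regression, baseline value or covariate is mentioned.

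Table 1 (Section 3.6.1) has a cost-effectiveness row, "Family utilization & cost data Administrative data", marked at baseline, post-treatment and 6-month follow-up. Height and weight are marked at the same three times.

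Section 5.1 analyses BMI percentile/z-score "using linear mixed effects (LME) analysis adjusting for corresponding baseline BMI percentile/z-score values". It adds: "All models will adjust for standard patient characteristics (age, race/ethnicity, sex, insurance type) as planned covariates", together with a clinic term. Baseline cost is not on that list.

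**The concern.** Where Section 5.1 intends baseline adjustment, it says so, both for the primary BMI model and for the mediator models. Section 5.2 instead commits to resampled means. Baseline cost is therefore collected with no stated use in the analysis.

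Precision is at stake, not bias. Chance differences between arms in prior resource use pass into the incremental cost to the extent that they predict later cost. They widen the bootstrap cloud and flatten the acceptability curve. Section 2 makes cost-effectiveness a secondary outcome with a directional hypothesis in favour of GSH, and no precision is stated for it. A free gain is worth taking.

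**Working it through.** **Inputs from the protocol article.** Section 5.3: 100 families per arm and up to 20% loss, so 100 × 0.8 = 80 analysed per arm. Section 5.2: 5000 resamples, effect measured as BMI units reduced.

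**Inputs assumed.** The article gives no correlation r between baseline and follow-up values. I take 0.2 to 0.6 for cost and 0.8 to 0.95 for BMI. The article states no cost standard deviation (SD) or precision for this analysis, so there is no figure of its own to reproduce.

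**Chance imbalance.** The difference between arms in any baseline mean has standard error √(2/80) = 0.158 baseline SDs.

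**Variances.** With follow-up variance 1 and equal variances at both times, the variance per family is:
- unadjusted follow-up value: 1
- change score: 2(1 − r)
- baseline-adjusted: 1 − r²

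**Incremental cost: unadjusted against baseline-adjusted.** The variance falls by r². The standard error (SE) ratio is 1/√(1 − r²), and the equivalent gain in sample size is 1/(1 − r²) − 1.

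| assumed r | variance reduction | SE ratio | equivalent extra families |
|---|---|---|---|
| 0.2 | 4% | 1.02 | 1/0.96 − 1 = 4% |
| 0.4 | 16% | 1.09 | 1/0.84 − 1 = 19% |
| 0.6 | 36% | 1.25 | 1/0.64 − 1 = 56% |

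These figures ignore the small price of estimating the coefficients. With 160 families and four covariates (baseline cost, clinic, sex, age), the variance is inflated by about 4/(160 − 4 − 3) = 4/153 = 2.6% if the covariates are roughly normal. At r = 0.2, if the other three predict nothing, the net variance is 0.96 × 1.026 = 0.985 of the unadjusted one, a gain of about 1.5%. At the low end the benefit is therefore close to nil.

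**Incremental effect: change score against baseline-adjusted.** The variance ratio, adjusted to change score, is (1 − r²)/[2(1 − r)] = (1 + r)/2.

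| assumed r | variance reduction | SE ratio (change/adjusted) |
|---|---|---|
| 0.8 | 10% | 1.054 |
| 0.9 | 5% | 1.026 |
| 0.95 | 2.5% | 1.013 |

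**Gap between change-score and adjusted BMI estimates on one scale.** Its SD is (1 − r) × 0.158 = 0.032, 0.016 and 0.008 BMI SDs at r = 0.8, 0.9 and 0.95.

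**The case against.** The strongest reply is that Section 5.2 never calls the means raw or unadjusted. A bootstrap works equally well on regression-adjusted means, the covariate sentence in Section 5.1 might be meant to reach the economic analysis, and a condensed article may leave such detail to a fuller plan. This stands in part: the unadjusted reading is the plain sense of the text, not an explicit statement. It does not settle the matter for cost, because baseline cost is missing from the Section 5.1 list even on the widest reading.

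Second, much of the cost may have no baseline counterpart. The delivery costs in Section 3.6.1 (materials, coaching and administrative time, IT support, patient time and expenditure to receive the intervention) arise only after randomisation. If they dominate, r is low and the gain is small. This stands.

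Third, a difference in bootstrapped means is a valid and conventional estimator in a randomised trial. Randomisation within clinic, stratified by sex, already limits imbalance on two of the covariates. This also stands, so no error is shown.

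Two stronger readings are tempting, and the text does not support them. A reader might infer a very large loss on the BMI side. At r = 0.8 to 0.95, comparing follow-up BMI means would give standard errors 1.67 to 3.20 times the adjusted ones. But the endpoint is a reduction, so baseline BMI is already used. A reader might also infer that the effect in the economic analysis is bound to disagree with the primary result through lack of adjustment. Under randomisation both estimators target the same difference on a given scale and part only by chance imbalance, by the small amounts shown above. The visible difference between Sections 5.1 and 5.2 is one of scale, BMI units against percentile/z-score, and covariate adjustment would not remove it.

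**Conclusion.** The point holds as a modest, optional precision improvement centred on cost. As written, Section 5.2 names no baseline adjustment although the baseline data are scheduled. The estimator is valid, but it leaves unused about 4% to 36% of the variance of the incremental cost, if the correlation lies between 0.2 and 0.6. That range is my assumption, and the lower part is the likelier one if delivery costs dominate. On the effect side the gain is 2.5% to 10% in variance, or about 1% to 5% in standard error, at assumed correlations of 0.95 to 0.8. No bias, invalid inference or wrong figure is demonstrated.

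**What to change.** In Section 5.2, state that within each of the 5000 resamples two regressions are fitted to the same resampled families, so that the link between cost and effect is kept:

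- total cost on arm, baseline cost, clinic, sex and age;
- the effectiveness outcome on arm, its baseline value and the Section 5.1 covariates.

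The two arm coefficients are the incremental cost and effect for the scatter plot, the intervals and the acceptability curve. Keep the unadjusted version as a sensitivity analysis. If the unadjusted analysis is intended as the main one, say so and give the reason.

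The cost is a sentence or two and a few lines of code. No new data or visits are needed.

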## Study objectives

2

The goal of the GOTDoc (**G**uided self-help **O**besity Treatment in the primary care setting) study is to test the effectiveness of the GSH model of obesity treatment compared to usual care (family-based behavioral weight control treatment (FBT) in a tertiary care setting) in 200 families with children with OW/OB between the ages of 5 and 13 years old. Research staff or health coaches will deliver GSH in the primary care setting and FBT at the UC San Diego Center for Healthy Eating and Activity Research (CHEAR). The intervention and data collection will occur from January 2017 to December 2019. Primary outcomes will include the proportion of treatment sessions families attend (GSH vs. usual care) and change in child BMI percentile/z-score. Secondary aims will include examination of change in child lifestyle behaviors, parent support behaviors, and parent self-efficacy and empowerment to make behavior changes. Cost-effectiveness of GSH on changes in child BMI percentile/z-score is also a secondary outcome. We hypothesize that there will be greater attendance of treatment in the GSH arm, and that among those who attend treatment, there will be similar changes in weight status between groups. However, because more families will attend GSH, we also hypothesize that in the intent to treat analysis GSH will have a greater impact on child BMI percentile/z-score than usual care (FBT). We also hypothesize that GSH will be more cost-effective than FBT.

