5.3. Power Analysis: For this trial, sample size estimates took attrition into account. Our first primary hypothesis is that a greater proportion of families in the intervention group will enter into and attend behavioral treatment for obesity. However, there was lack of evidence from previous studies to conduct a power analysis with this outcome. Therefore, power analyses were based on changes in BMI z-score (our second primary outcome) that was supported by observations in the GSH pilot which estimated a decrease in BMI z-score d = |1.71–1.50|/.30 = 0.667. Empirical power estimates were assessed by generating multivariate random samples that were matched to the expected BMI z-score for each condition and variability over time as observed in our pilot study. We expected decreases in BMI z-score of 0.10 among those enrolling in GSH, and a slight increase of 0.05 in BMI z-score in the usual care group. Each of 1000 simulated data sets was analyzed using a LME (random intercepts: patients within clinics) and specific output saved (e.g., standardized regression coefficients, p-values). The percentage of datasets with significant effects (i.e., p < 0.05) for the primary hypothesis comparing GSH vs. usual care provided a simulation-based estimate of power for the primary hypothesis. With a median between-group effect of −0.39 (s d. = 0.13) across 1000 data sets, the planned design would provide greater than 0.82 power for detecting the effect with allowance for up to 20% lost to follow up [72]. We allow up to 20% loss to follow-up to maintain the integrity of the sample for data analysis, and have been able to limit our loss to follow-up in previous trials to 13–18% of the sample. Given these parameters, we estimated that we would need to recruit 200 families into the trial, 100 in GSH and 100 in FBT. With a sample of 200 to support between-group comparisons of BMI percentile/z-score, we estimate we will have power >0.95 to detect a difference in the proportion of sessions attended in a generalized linear model (binomial) with two-sided alpha <0.05 given that we expect >85% attendance in GSH and 60% attendance in FBT. All analyses of primary outcomes will use an intention to treat sample with analyses of all participants who provided both baseline and post-treatment assessments.

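### Section 5.2 derives the ICER by permutation, which imposes no difference between arms and conflicts with the bootstrap described in the next sentence

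*Protocol article*

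**What the plan says.** Section 5.2 of the protocol article sets the target of the cost-effectiveness analysis: "The final outcome of the CEA in this study is the cost per BMI unit reduced", comparing GSH with usual care through incremental differences. On method it says, in this order:

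- For the components: "we will use bootstrap to create confidence intervals for the mean costs and effectiveness for the comparison".
- For the ratio: "ICER will be developed using the nonparametric permutation".
- For its display: "A scatter plot of 5000 bootstrapped ICER will be generated by drawing a random sample with replacement".
- For the summary: "The CEA results will be presented in a cost-effectiveness acceptability curve".

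It also plans sensitivity analyses. It plans no confidence interval for the ICER itself, and it does not say which set of replicates feeds the acceptability curve.

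**The concern.** A permutation reassigns families to arms at random. It answers what differences would look like if the arm made no difference, which suits a test of the null hypothesis. An ICER needs the differences that were observed, and its uncertainty needs a distribution centred on them. The sentence therefore names a procedure that cannot deliver the quantity it is meant to deliver, and the next sentence names another.

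A smaller issue is the display. The replicates are described as ICERs, not as pairs of cost and effect differences. A negative ratio arises both when GSH is cheaper and better and when it is dearer and worse, so ratios alone lose the information on which the conclusion depends.

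At stake is a declared secondary outcome with its own hypothesis, which the Discussion says will matter to health systems and insurers. An analyst who followed the permutation sentence, or fed permuted draws into the acceptability curve, would report results that do not reflect the trial's data.

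**Working it through.** Section 5.2 gives no numerical result to reproduce, so the check is of the method.

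**1. What permutation does.** Pool all families and draw one arm's worth at random. The expected mean of any random subset is the pooled mean, so the expected difference between the two relabelled arms is pooled mean minus pooled mean = 0. This holds for cost and for effect, whatever the true values are.

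**2. Simulation.** Inputs from section 5.3: 100 per arm with up to 20% loss, so 100 × 0.80 = 80 per arm; standardised effect 0.39, from "With a median between-group effect of −0.39 (s d. = 0.13) across 1000 data sets". Assumed, because the article gives no costs: mean cost 1000 (SD 400) in GSH and 1500 (SD 600) in FBT. There were 5000 replicates of each kind. Effect is in SD units, with positive values favouring GSH.

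| | Set in the simulated data | Within-arm bootstrap | Permutation |
|---|---|---|---|
| Mean cost difference | -500 | -498 | 1 |
| Mean effect difference | 0.39 | 0.391 | 0.000 |
| Share of effect differences at or below 0 | – | 0.6% | 51% |
| Acceptability curve, thresholds 0 to 20000 | – | 0.996 to 1.00 | 0.49 to 0.50 |

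The bootstrap curve values depend on the assumed costs. The centring of permutation on zero, and its curve near one half, do not.

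**3. The sign of the ratio.** With cost difference -c and effect difference +e, the ratio is -c/e. With +c and -e it is also -c/e. The two opposite conclusions share one number, and only the pair separates them.

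**4. How likely a sign change in the denominator is.** The planning inputs are in section 5.3: "We expected decreases in BMI z-score of 0.10 among those enrolling in GSH, and a slight increase of 0.05 in BMI z-score" in usual care, a difference of 0.10 + 0.05 = 0.15 z. Dividing by the standardised effect gives an implied SD of 0.15 / 0.39 = 0.385. The standard error at 80 per arm is 0.385 × √(2/80) = 0.385 × 0.158 = 0.061. By the normal approximation, P(effect difference < 0) = Φ(-difference / SE):

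- true difference 0.15 z: Φ(-0.15/0.061) = 0.7%
- true difference 0.05 z (assumed): Φ(-0.05/0.061) = 21%

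On the standardised scale, with SE 0.158, the range is 0.7% at 0.39, 10% at 0.2, 26% at 0.1 and 50% at 0. If the spread of 0.13 given in section 5.3 is used as the SE, the figure at 0.39 is Φ(-3.0) = 0.1%.

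The z-score stands in for the BMI unit of section 5.2, for which the article gives no SD.

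**5. Does the planned curve survive a small effect?** Yes, if it is built from bootstrap pairs. With a true effect of 0 the simulated bootstrap curve was still well defined, for example 0.73 at a threshold of 5000 under the assumed costs.

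**The case against.** The strongest reply is that the word is a slip. The section calls for bootstrap before the sentence and describes draws with replacement after it. It describes no shuffling of labels, and the only procedure it spells out is a bootstrap. A scatter plot has two axes, so a plot of ICERs is naturally read as shorthand for cost-effect pairs. The bootstrap intervals for mean cost and effectiveness and the acceptability curve do not need a stable ratio. The text is also a condensed article.

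Most of this stands. It lowers the likelihood of harm, but it does not make the sentence correct. The article does not leave the method to another document; it names one, and the one it names cannot do the job.

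A reader might infer more than the article supports:

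- *That the conclusion would rest on an invalid confidence interval for the ICER.* No such interval is planned.
- *That the ratio is bound to break down because the arms are expected to be alike.* Section 2 says "among those who attend treatment, there will be similar changes in weight status between groups", but this is limited to attenders. The sentence after it expects a greater effect of GSH under intention to treat. At the planning difference a sign change is improbable.
- *That the protocol expects GSH to be both cheaper and better.* Section 2 expects a greater intention-to-treat effect and better cost-effectiveness; it never says that GSH will cost less.
- *That the size of the error can be put in dollars.* The article gives no costs, so any dollar limits for the ICER would reflect only the costs assumed.

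**Conclusion.** The permutation sentence is wrong as written and contradicts the sentence after it. It would centre the cost and effect differences on zero in any data set, and this conclusion needs no assumption about costs or effect size. The rest of the planned analysis is sound provided that it uses bootstrap draws.

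Instability of the ratio is a secondary argument for plotting pairs. It is negligible at the planning effect (0.1% to 0.7%) and becomes material only if the true difference is much smaller (about 21% at an assumed 0.05 z). These figures rest on 80 per arm, an implied SD of 0.385 and a normal approximation.

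The point concerns a secondary outcome. The sample size and both primary analyses are unaffected. It should be corrected before the economic analysis is run.

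**What to change.** In section 5.2:

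1. Delete the permutation sentence.
2. Define the ICER as the ratio of the observed intention-to-treat mean differences in cost and effect.
3. State that the 5000 bootstrap samples are drawn by resampling families with replacement within arm, keeping each family's cost and effect together.
4. Plot the resulting pairs of differences on the cost-effectiveness plane instead of the ratios.
5. Compute the planned acceptability curve from the same draws.
6. If one arm proves both cheaper and more effective, say so in words and do not report a negative ICER.

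The cost is a few sentences of text and a few lines of code. No new data are needed, and there is no change to sample size, schedule or primary analyses.
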